**Fig. 1 Fig1:**
[figure not shown]
Flow chart of the COMPASS study

**Table 3 Tab3:**
[figure not shown]
Schedule for the COMPASS study

### Sample size {14}

Taking the effects obtained in the article *Effects of a group psychoeducation program on self-stigma, empowerment and perceived discrimination of persons with schizophrenia* [72], for the TAU and ESS groups and adding a CFT group with a stronger and lasting effect, the means and standard deviations of the ISMI before the therapy, after the therapy, and after 6 months follow-up used to estimate the sample size are respectively 2.46 ± 0.39, 2.43 ± 0.29, and 2.46 ± 0.39 for the TAU group; 2.45 ± 0.48, 2.20 ± 0.41, and 2.40 ± 0.48 for the psychoeducation group; and 2.45 ± 0.48, 2.10 ± 0.41, and 2.20 ± 0.48 for the CFT group. With 84 patients in each group, the power is more than 85% between the TAU and psychoeducation groups after the therapy and more than 99% between CFT and the other groups after 6 months. In order to consider the possible loss to follow-up, the sample size is increased by 33% to obtain 112 patients in each group. The total sample size is therefore 336 participants.

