#### Objectives {7}

The primary objective of our study is to evaluate the efficacy of a 12-week CFT group in decreasing self-stigma associated with severe psychiatric disorders and ASD by comparing its immediate effects to the effects of the Ending Self-Stigma (ESS) psychoeducation program [29] and to TAU.

The secondary objectives of our study are as follows:1. To evaluate the maintenance of effects on self-stigma scores in the three groups of treatment (CFT, ESS, and TAU) at 6-month follow-up (V2)2. To assess the effects of treatment (CFT, ESS, and TAU) at baseline (V0), post-treatment (V1), and at 6 months follow-up (V2) on target psychological dimensions (shame, self-compassion, emotional regulation, automatic avoidance tendencies toward mental illness)3. To assess the effects of treatment (CFT, ESS, and TAU) at baseline (V0), post-treatment (V1), and at 6 months follow-up (V2), on social functioning and psychiatric measures (psychiatric symptoms, depression, anxiety and stress, social functioning, access to care, recovery, functional remission)4. To assess the psychological factors mediating (shame, self-compassion, and emotional dysregulation) the efficacy of CFT on the self-stigma measure (V1)5. To evaluate the acceptability of the active interventions (CFT and ESS): pretreatment (V0) via a treatment credibility measure, during treatment via attrition rate, session attendance and group cohesion, and post-treatment (V1) via patient satisfaction and treatment side effects In addition, in the coordinating center, qualitative interviews will assess the acceptability of the active interventions.

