### Outcomes {12}

#### Primary outcomes

The decrease in scores on the Internalized Stigma of Mental Illness Scale (ISMI) [31] will be our primary outcome. The ISMI scale has good psychometric qualities in its various language versions [20]. This measure is a 29-item self-report questionnaire with five subscales: (1) alienation, (2) endorsement of perceived stereotypes, (3) discrimination, (4) social withdrawal, and (5) resistance to stigma. The participant must select their response on a 4-point Likert scale ranging from strongly disagree (1) to strongly agree (4).

The ISMI scale will be administered before therapy (V0), at the end of therapy (V1), and 6 months after the end of therapy (V2). If CFT is efficacious in reducing self-stigma, ISMI scores will decrease significantly between V0 and V1, and this decrease will be greater for CFT than for psychoeducation (ESS) and TAU.

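### The power statement omits both primary post-treatment contrasts (CFT-ESS has about 35% power unadjusted), and its 6-month figure of over 99% is not supported against ESS (77% unadjusted)

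*Protocol article*

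**What the plan says.** Under Objectives {7}, the primary objective is to evaluate CFT "by comparing its immediate effects to the effects of the Ending Self-Stigma (ESS) psychoeducation program [29] and to TAU". Under Primary outcomes, the prediction for the change from V0 to V1 is that "this decrease will be greater for CFT than for psychoeducation (ESS) and TAU". There are therefore two primary contrasts at V1: CFT against ESS and CFT against TAU. The 6-month comparison is the first secondary objective: "To evaluate the maintenance of effects on self-stigma scores in the three groups of treatment (CFT, ESS, and TAU) at 6-month follow-up (V2").

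Sample size {14} lists assumed ISMI means and SDs at V0, V1 and V2: "2.46 ± 0.39, 2.43 ± 0.29, and 2.46 ± 0.39 for the TAU group"; "2.45 ± 0.48, 2.20 ± 0.41, and 2.40 ± 0.48 for the psychoeducation group"; and, for CFT, 2.45 (SD 0.48), 2.10 (SD 0.41) and 2.20 (SD 0.48). With 84 per group it then gives two power figures. The first is "the power is more than 85% between the TAU and psychoeducation groups after the therapy". The second is "more than 99% between CFT and the other groups after 6 months". The 84 is raised to 112 per group for loss to follow-up. The section names no test, significance level or correlation between visits.

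**The concern.** Neither power figure addresses the primary question. The first compares the two control arms. The second concerns CFT, but at the secondary time point. Yet the section prints every mean and SD needed for the V1 contrasts, and the assumed CFT-ESS difference there is small: 0.10 points against an SD of 0.41. The 6-month figure also looks too high for a 0.20-point difference with an SD of 0.48.

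The stakes lie in interpretation. If the planning assumptions are exactly right, the comparison with the active control at the primary time point is more likely than not to miss the decision threshold, unless the baseline correlation is well above 0.5. Without a stated power for that contrast, a reader could take a null result as evidence that the two programmes work equally well.

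**Working it through.** **Inputs.** Means, SDs and n = 84 per arm come from Sample size {14}. The level is my assumption: two-sided 5%. The section states none, and the posterior-probability rule of 0.975/0.025 under Statistical methods {20a} behaves similarly with weak priors and a threshold of zero.

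**Formula (unadjusted).** SE = √[(s₁² + s₂²)/n]; power ≈ Φ(difference/SE − 1.96). The noncentral t gives values at most 0.5 points lower.

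**The plan's own figures first.**

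- TAU-ESS at V1: difference 2.43 − 2.20 = 0.23; SE = √[(0.29² + 0.41²)/84] = 0.0548; ratio 4.20; power 98.7%. The stated lower bound of 85% is met.
- CFT-ESS at 6 months: difference 2.40 − 2.20 = 0.20; SE = √[(0.48² + 0.48²)/84] = 0.0741; ratio 2.70; power 77.0% (76.6% by noncentral t). The stated figure is not reproduced.
- CFT-TAU at 6 months: difference 2.46 − 2.20 = 0.26; SE = √[(0.48² + 0.39²)/84] = 0.0675; ratio 3.85; power 97.1% (96.9% by noncentral t). This falls slightly short.

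**Other unadjusted readings of the 6-month claim.** None reaches 99% for CFT-ESS:

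| Reading | Power |
|---|---|
| CFT-ESS, one-sided 5%, n = 84 | 85.4% |
| CFT-ESS, two-sided 5%, n = 112 | 87.7% |
| CFT-ESS, one-sided 5%, n = 112 | 93.0% |
| CFT against ESS and TAU pooled, 84 per arm | 95.8% |
| Three-group ANOVA, 84 per arm | 94.5% |

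**The omitted primary contrasts at V1.**

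- CFT-TAU: difference 2.43 − 2.10 = 0.33; SE 0.0548; ratio 6.02; power above 99.9%.
- CFT-ESS: difference 2.20 − 2.10 = 0.10; SE = √[(0.41² + 0.41²)/84] = 0.0633; ratio 1.58; power 35.2% (34.9% by noncentral t). With all 112 per arm it is 44.6%.
- Difference detectable with 80% power: (1.96 + 0.84) × 0.0633 = 0.18 points, against the 0.10 assumed.

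**Using the baseline.** With correlation r, ANCOVA multiplies each SD by √(1 − r²). A change score has SD √(s₀² + s₁² − 2r·s₀·s₁).

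| Contrast | Method | r | Power |
|---|---|---|---|
| CFT-ESS, V1 | ANCOVA | 0.5 | about 44% |
| CFT-ESS, V1 | ANCOVA | 0.7 | 60% |
| CFT-ESS, V1 | ANCOVA | 0.8 | 75% |
| CFT-ESS, 6 months | ANCOVA | 0.78 | first reaches 99% |
| CFT-ESS, 6 months | change score | 0.81 | first reaches 99% |
| CFT-TAU, 6 months | ANCOVA | about 0.45 | reaches 99% |

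If the same correlation holds at V1, the values that bring CFT-ESS to 99% at 6 months still leave CFT-ESS at V1 at about 71% (ANCOVA, r = 0.78) or 63% (change score, r = 0.81). Reaching 80% at V1 would take r of about 0.83 (ANCOVA) or 0.88 (change score).

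**The case against.** The strongest reply is that the planned analysis is not an unadjusted comparison of means. Statistical methods {20a} plans a regression with subject as a random effect, and ISMI is measured at all three visits, so within-person correlation can add power. The article states no test or correlation, and the full protocol is not shown. This stands in part. The 35% needs its assumptions beside it and belongs in a range. The 6-month figure against ESS is best called unsupported as printed, since a correlation of about 0.78 or more would yield it. For CFT-TAU at 6 months, a correlation of about 0.45 is enough, so that gap is minor.

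Three stronger readings are tempting and do not hold.

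- A reader might infer that the 85% figure is also wrong, because the larger standardised effect carries the smaller stated power. It is a lower bound, and 98.7% satisfies it.
- A reader might infer that the plan claims 85% to 99% power for its primary comparison. It does not: each figure is tied to named groups and a time point, and the fault for V1 is omission.
- A reader might infer that the trial as a whole is underpowered for its primary objective. The documents name ESS and TAU side by side without ranking them, and CFT-TAU at V1 is amply powered. The weakness is confined to CFT-ESS.

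It can also be said that 95% credibility intervals are already promised, so the estimate will be reported in any case. That is so, but it does not tell readers how little a null CFT-ESS result would show.

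**Conclusion.** The point holds in this form. The sample-size section gives no power for either primary contrast. On its own inputs, CFT-TAU at V1 exceeds 99.9%, while CFT-ESS at V1 is about 35% unadjusted and about 44% to 75% under ANCOVA with r from 0.5 to 0.8. The claim of more than 99% at 6 months is unsupported against ESS (77% unadjusted). The correlation needed to rescue it is high, is not stated, and would still leave CFT-ESS at V1 below 80%.

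These results assume a two-sided 5% level, 84 evaluable patients per arm, the printed means and SDs, and independent observations. Therapy is delivered in groups of 8, and the section makes no allowance for clustering within groups; any such correlation would lower the powers further.

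**What to change.** Rewrite the power sentence in Sample size {14}:

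1. Give V1 power for both primary contrasts, with the test, alpha and assumed baseline correlation: CFT-TAU above 99.9%; CFT-ESS about 35% unadjusted at 84 per arm, with a detectable difference of about 0.18 points at 80% power. If baseline adjustment is assumed, give the adjusted power beside its correlation.
2. Replace the 6-month figure against ESS with 77% unadjusted, or state the correlation and method that justify a higher value. Give CFT-TAU at 6 months on the same basis (97% unadjusted). The TAU-ESS figure may stay.
3. Add that a non-significant CFT-ESS result at V1 will not be read as equal efficacy.

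This is a change of wording only. It needs no extra patients and no change of procedure. The cost is a less favourable stated power; the actual power for CFT-ESS does not change, but readers will know what it is.

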### Recruitment {15}

A large network of professionals in institutions or in private practice (e.g., psychiatrists, psychologists) of the geographical area of all the participating centers of the study will be deployed to refer patients to the investigating teams. All the hospital centers are central coordinators of the care of patients with SMI and ASD in their respective areas; moreover, all of them propose care within a recovery model of psychiatric disorders. These factors guarantee that many patients with SMI and ASD can be recruited in these centers and that all centers will show high levels of implication in the recruitment and adherence to the psychotherapeutic models proposed.

Patients will be recruited into the psychiatric and mental health department of each center during a routine clinical consultation. The inclusion period is 48 months. This is a realistic duration given the significant number of patients to be enrolled. The study is scheduled to involve 7 French national centers, with 24 patients to be enrolled per center (one randomization blocks of 24 patients—3 groups of 8 patients in CFT, ESS, and TAU—in each center; the Strasbourg center will recruit 192 patients, i.e., 8 randomization blocks).

### Assignment of interventions: allocation

#### Sequence generation {16a}

Randomization will be done through the CleanWEB® platform, which will be accessed by the investigator or a designated person, using their personal access codes. The investigating team and the sponsor will receive an email confirming the randomization. Patients will be randomized over a period of 1 month before the start of the interventions, to allow the 3 groups of treatment to be formed (CFT, ESS, TAU), so that each group starts the allocated therapy at the same time.

The randomization will be stratified by center, with a 1:1 ratio for allocation to the 3 groups. Patients will be recruited until they form a group of 24 people allowing to randomize them in one of the 3 conditions, in groups of 8 people matched on gender and diagnostic group (4 possibilities: (1) psychotic disorder, (2) mood disorder, (3) personality disorder, and (4) autism spectrum disorder, referring to (1) schizophrenia-spectrum disorder, (2) bipolar disorder and depression, (3) borderline personality disorder, and (4) autism spectrum disorder). This process will be reiterated at least once in each center:

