## Statistical methods

### Statistical methods for primary and secondary outcomes {20a}

The statistical analysis will have descriptive and inferential. The analyses will be carried out according to Bayesian methods.

The descriptive statistical analysis of the categorical variables will be performed by giving the frequencies, the cumulative frequencies, the proportions, and the cumulative proportions of each value. Whenever useful, cross-tabulations will be given with frequencies, proportions by row, proportions by column, and proportions of the total for each box in the table. For each continuous variable, the location parameters (mean, median, minimum, maximum, first and third quartiles) and the dispersion parameters (variance, standard deviation, range, interquartile range) will be given. The continuous variables will be described with histograms (with different bin width and with kernel density estimation). The normality of the distributions will be tested using a normality test, such as the Shapiro-Wilk test, and will be assessed graphically using a normal quantile plot.

To fulfill the primary objective, a generalized Bayesian linear regression model will be performed in order to estimate the effect of the treatment considering the center and the subject as a random effect. According to the distribution of the primary endpoint, i.e., the ISMI, the linear regression will be Gaussian, beta, or gamma.

To fulfill the secondary objectives, a generalized Bayesian linear regressions model will be performed: binary variables will be analyzed with a Bayesian logistic regression, score variables will be analyzed with a Bayesian beta regression, count variables will be analyzed with a Bayesian Poisson regression, and continuous variables will be analyzed with a Bayesian linear regression.

Priors will be firstly weakly informative and secondly more informative in a sensitivity analysis.

For each analysis, the posterior distribution of the parameter of interest (rate, proportion, mean, odds-ratio, regression coefficient, etc.) will be estimated using Markov chain Monte Carlo (MCMC) draws. The default number of iterations is 100,000 with a burn-in of 10,000 and a thinning of 2 on each of 3 chains. Algorithm convergence will be assessed graphically and with the Gelman-Brooks-Rubin (GBR) test. Autocorrelation will be assessed graphically, and if required, the number of iterations and thinning will be increased to reduce as much as possible the autocorrelation.

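### Allocation is matched on gender and diagnostic group, but the stated primary model names neither; reported uncertainty may be slightly too wide, and naming them costs little

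*Protocol article*

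**What the plan says.** Under Sequence generation {16a}: "The randomization will be stratified by center, with a 1:1 ratio for allocation to the 3 groups". The same paragraph adds a further constraint. Patients accumulate until there are 24, who are then allocated to the three arms "in groups of 8 people matched on gender and diagnostic group". The diagnostic groups are psychotic, mood, (borderline) personality and autism spectrum disorder. Recruitment {15} implies one such block in each of six centres and eight in the coordinating centre.

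Under Statistical methods for primary and secondary outcomes {20a}, the primary objective is met by a Bayesian regression to "estimate the effect of the treatment considering the center and the subject as a random effect". Gender, diagnostic group and block are not named there or elsewhere in the statistical sections. Methods for additional analyses {20b} says that none are planned, so no adjusted analysis is described as a supplement.

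ISMI is measured at V0, V1 and V2 (Primary outcomes). An effect is declared when its posterior probability passes 0.975 or falls below 0.025 ({20a}).

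**The concern.** The article states a model that carries one allocation factor, centre, and leaves out the other two. When arms are balanced by design on factors that predict the outcome, a model without those factors assigns their variance to residual noise. The reported interval is then wider than the design warrants, and a fixed 0.975 threshold becomes harder to pass than intended.

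The balance also belongs to the patients randomised. Sample size {14} allows for going from 112 to 84 per arm, and nothing keeps the 84 matched. Conditioning on the two factors would guard against a chance or differential shift in diagnostic mix after dropout. The Discussion itself expects that mix to vary between centres.

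**Working it through.** **1. Allocation and model side by side**

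| Factor | Used in allocation {16a} | Named in primary model {20a} |
|---|---|---|
| Centre | yes (stratified) | yes (random effect) |
| Gender | yes (matched) | no |
| Diagnostic group, 4 levels | yes (matched) | no |
| Block of 24 | yes | no |

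**2. The plan's own figures**

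The article gives no figure for precision from gender or diagnosis, so there is none to reproduce on this point. The sample size arithmetic agrees: 84 × 1.33 = 111.7 and 84/0.75 = 112 per arm; 6 × 24 + 192 = 336. The inflation equals 25% loss.

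For scale, take CFT against ESS at V1. The inputs in {14} are "2.45 ± 0.48, 2.20 ± 0.41, and 2.40 ± 0.48 for the psychoeducation group" and "2.45 ± 0.48, 2.10 ± 0.41, and 2.20 ± 0.48 for the CFT group". The difference is 2.20 − 2.10 = 0.10, the SD is 0.41 and n = 84.
- SE = 0.41 × √(2/84) = 0.0633
- Power = Φ(0.10/0.0633 − 1.96) = 35.2%, reading the 0.975/0.025 rule as two-sided 0.05

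**3. Model of V1 alone**

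Let R² be the share of ISMI variance explained by gender and diagnosis. The documents do not give it; 0.02 to 0.15 is assumed. Adjusted SE / unadjusted SE = √(1 − R²).

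| R² | SE ratio | Power, CFT vs ESS at V1 (35.2% unadjusted) |
|---|---|---|
| 0.02 | 0.990 | 35.8% |
| 0.05 | 0.975 | 36.8% |
| 0.10 | 0.949 | 38.4% |
| 0.15 | 0.922 | 40.3% |

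**4. Model that uses V0**

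This is closer to the stated model, which has a subject effect. Let ρ be the V0-V1 correlation (assumed 0.5 to 0.7), with the factors acting equally at both visits.
- Residual variance without the factors: 1 − ρ²
- Residual variance with them: (1 − R²)(1 − r²), where r = (ρ − R²)/(1 − R²)

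Example, ρ = 0.5 and R² = 0.15: r = 0.35/0.85 = 0.412; variance = 0.85 × 0.830 = 0.706 against 0.750; SE ratio = √(0.706/0.750) = 0.970.

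| R² | SE ratio, ρ = 0.5 | Power (44.6% unadjusted) | SE ratio, ρ = 0.7 | Power (60.0% unadjusted) |
|---|---|---|---|---|
| 0.02 | 0.997 | 44.9% | 0.998 | 60.2% |
| 0.05 | 0.991 | 45.3% | 0.995 | 60.4% |
| 0.10 | 0.981 | 46.0% | 0.990 | 60.9% |
| 0.15 | 0.970 | 46.9% | 0.984 | 61.4% |

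**5. Pure V0-to-V1 change contrast**

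A factor that shifts only a patient's stable level cancels in the difference. The SE ratio is 1.00.

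**6. Is the estimate or its stated uncertainty affected?**

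This was simulated with 1,500 runs, 80 per arm, allocation exactly matched within the 2 × 4 = 8 gender-by-diagnosis cells, R² = 0.15 and ρ = 0.7.

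| Model | Actual SD of CFT − ESS estimate | Reported SE |
|---|---|---|
| V1 only, unadjusted | 0.0597 | 0.0649 |
| V1 only, adjusted | 0.0597 | 0.0598 |
| With V0 as covariate, unadjusted | 0.0463 | 0.0464 |
| With V0 as covariate, adjusted | 0.0462 | 0.0457 |
| Change score, either way | 0.0513 | 0.0502 |

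The estimate varies by the same amount with or without the factors. Only the reported SE moves. Once V0 is used, the gap is within simulation noise at ρ = 0.7.

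**The case against.** The strongest reply is that one condensed sentence in a journal article is being treated as a complete model. It does not say that no other terms enter, and a covariate list is commonly left to the analysis plan, which is not shown. This stands in part: a reader might infer that gender and diagnosis are excluded, and the text does not support that. What remains is that the sentence names one allocation factor and omits two, so an analysis that follows it literally would leave them out.

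The second reply is that the subject effect and V0 already absorb most of what two time-fixed factors contribute. This is right, and it is why the gain shrinks from as much as 8% of the SE to 0-3%.

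The third is that matching delivers its benefit through the design. This is also right. A reader might infer that the trial throws away precision which the matching was built to provide. Step 6 shows that the estimate keeps its precision, and the article never says why it matches; a balanced mix of patients in the therapy groups is an equally plausible reason. Exact matching would need multiples of three patients in each of eight cells in every block of 24, so it is probably approximate, which shrinks the effect further.

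The planned intention-to-treat analysis and missing-data handling ({20c}) soften the dropout argument without removing it, since neither is said to condition on gender or diagnosis.

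**Conclusion.** The mismatch is real and minor. As stated, the primary model omits two factors that constrain allocation. If they predict ISMI, its posterior SD is somewhat too wide. The error is conservative: it does not bias the estimate or raise the false-positive rate.

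The likely size is a 0 to 3% reduction in the SE, or 0.2 to 2.3 points of power for CFT against ESS in the covariate-type model. It reaches about 8% only if neither V0 nor the subject effect is used. These figures rest on assumed R² of 0.02 to 0.15, assumed ρ of 0.5 to 0.7, a Gaussian model and close matching; none of these comes from the documents except the Gaussian option.

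A reader might also infer that adjustment would rescue the CFT-ESS comparison. It would not: even the most favourable case in step 3 moves power only from 35.2% to 40.3%.

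**What to change.** In {20a}, name gender (one term) and diagnostic group (three terms) as fixed effects in the primary ISMI model, or say why they are omitted. Both must be known at allocation, so no new data are needed.

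Optionally add randomisation block as a random effect nested in centre. There are 6 + 8 = 14 blocks, and in six of the seven centres block and centre coincide, so the term is informative only in the coordinating centre.

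The cost is four parameters, plus one variance component if block is added as a random effect. Blocks entered as fixed terms would instead add 14 − 7 = 7 parameters beyond centre. The change is best confined to the primary ISMI model: in the logistic models planned for binary secondary outcomes, added covariates change the odds ratio being estimated, which would need its own justification.
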